## Abstract

**Background:**

Chagas disease (CD) is a neglected endemic disease with worldwide impact due to migration. Approximately 50–70% of individuals in the chronic phase of CD present the indeterminate form, characterized by parasitological and/or serological evidence of *Trypanosoma cruzi* infection, but without clinical signs and symptoms. Subclinical abnormalities have been reported in indeterminate form of CD, including pro-inflammatory states and alterations in cardiac function, biomarkers and autonomic modulation. Moreover, individuals with CD are usually impacted on their personal and professional life, making social insertion difficult and impacting their mental health and quality of life (QoL). Physical exercise has been acknowledged as an important strategy to prevent and control numerous chronic-degenerative diseases, but unexplored in individuals with the indeterminate form of CD. The PEDI-CHAGAS study (which stands for “Home-Based Exercise Program in the Indeterminate Form of Chagas Disease” in Portuguese) aims to evaluate the effects of a home-based exercise program on physical and mental health outcomes in individuals with indeterminate form of CD.

**Methods and design:**

The PEDI-CHAGAS is a two-arm (exercise and control) phase 3 superiority randomized clinical trial including patients with indeterminate form of CD. The exclusion criteria are <18 years old, evidence of non-Chagasic cardiomyopathy, musculoskeletal or cognitive limitations that preclude the realization of exercise protocol, clinical contraindication for regular exercise, and regular physical exercise (≥1 × per week). Participants will be assessed at baseline, and after three and 6 months of follow-up. The primary outcome will be QoL. Secondary outcomes will include blood pressure, physical fitness components, nutritional status, fatigability, autonomic modulation, cardiac morphology and function, low back pain, depression and anxiety, stress, sleep quality, medication use and adherence, and biochemical, inflammatory and cardiac biomarkers. Participants in the intervention group will undergo a home-based exercise program whilst those in the control group will receive only general information regarding the benefits of physical activity. Both groups will receive the same general nutritional counseling consisting of general orientations about healthy diets.

**Conclusion:**

The findings from the present study may support public health intervention strategies to improve physical and mental health parameters to be implemented more effectively in this population.

**Clinical trial registration:**

[https://ensaiosclinicos.gov.br/rg/RBR-10yxgcr9/], identifier [U1111-1263-0153].

## Introduction

Chagas disease (CD)—a parasitic infection caused by the flagellate protozoan *Trypanosoma cruzi* firstly described by the Brazilian physician Carlos Chagas in Chagas (1) and also known as American trypanosomiasis—is a neglected disease considered a major public health problem mainly for vulnerable populations, affecting endemic regions such as Latin American countries, and also regions such as Europe and the United States in which the prevalence of CD has increased over the last years due migration movements (2, 3).

The clinical course of CD occurs through two distinct phases: acute and chronic (4, 5). The acute phase is characterized mainly by the absence of symptoms or by the presence of mild or non-specific symptoms such as prolonged fever, malaise, headache, and enlarged lymph nodes. Specifically, when vector transmission occurs, entrance signals such as inoculation chagoma (in the skin) and Romaña signal (in the membrane of the ocular mucosa) may be present, but are rare. Mortality during this phase is ∼5% and occurs mainly due to acute myocarditis or meningoencephalitis. After the acute phase, which lasts around 4 to 8 weeks, the chronic phase ensues unless patients are diagnosed and effectively treated during the acute phase. Patients with chronic CD present clinical manifestations that vary from the absence of specific signs and/or symptoms related to the disease to different degrees of impairments in the heart, esophagus, and/or intestine, that may happen isolated or combined (6). Thus, the chronic phase of CD can be categorized into four different forms according to the clinical characteristics as follows: indeterminate, cardiac, digestive, and mixed (cardio-digestive) forms (4, 5).

Approximately 50–70% of individuals with chronic CD present the indeterminate form of the disease, characterized by parasitological and/or serological evidence of *T. cruzi* infection, but absence of major clinical signs and symptoms, normal electrocardiogram, and normal chest, esophagus and colon X-rays (7, 8). However, the indeterminate form can progress to the determinate forms of CD, with an estimated annual progression rate of 1.9% (9, 10). Most infected individuals will remain in the indeterminate form for the rest of their life, with a benign prognosis (4, 11, 12). However, subclinical abnormalities have also been observed in patients with indeterminate form of CD in comparison to those without CD, including early cardiac abnormalities (e.g., greater fibrosis mass) (13, 14), changes in biomarkers of the inflammatory profile and cardiac function (15–17), and alterations of autonomic modulation (18–21). The prognostic value of most of these early subclinical abnormalities is still not determined, although a recent study that evaluated parameters derived from two-dimensional strain provided independent predictors progression to Chagas cardiomyopathy in patients with the indeterminate form of CD (10).

Considering that CD is a neglected disease, more prevalent among people with low socioeconomic status, individuals with CD are usually impacted on their personal and professional life since they are frequently labeled as vulnerable and limited in several aspects, making social insertion difficult, and impacting their mental health and physical and psychological domains of quality of life (QoL) (22–25). The decrease in QoL is associated with an increase in the symptoms of depression and worsening of the perception of health (26, 27). Few studies have evaluated impact of CD on mental health, mostly focusing on cardiac and digestive forms, usually excluding participants with indeterminate form of CD. Thus, comprehensive interventions to improve different parameters of the physical and mental health of individuals with indeterminate form of CD are necessary.

Physical exercise has been used as an important well-established tool for prevention and control of numerous chronic-degenerative diseases in different populations (28). Compelling evidence has shown that increasing physical activity levels is associated with lower mortality in individuals with and without diseases (29, 30). Other benefits from physical activity include increase in functional capacity, weight control, improvement in pain, better mental health (including depression and anxiety) and QoL (31, 32), anti-inflammatory profile, oxidative capacity, endothelial function, autonomic modulation, and cardiopulmonary and musculoskeletal capacity (33–35).

However, despite the well-recognized benefits, the adherence to conventional supervised exercise programs is low, with approximately 50% of the individuals interrupting such programs in the first 6 months (36, 37). Numerous strategies have been investigated to improve adherence to regular physical activity and home-based exercise has emerged as a good alternative. Besides being a low-cost strategy, which is a great advantage for individuals with CD due to its low socioeconomic level and reduced access to supervised exercise programs, home-based exercise allows more flexibility in deciding when exercise, facilitating adherence (38, 39). Moreover, the effects of physical exercise in individuals with CD have not been explored consistently in the literature. Some previous studies presented promising results for the improvement of cardiac function, functional capacity and QoL in patients with cardiac form of CD, but studies evaluating the effect of physical exercise on health parameters in individuals with indeterminate form of CD are still scarce in the literature (40–44). The PEDI-CHAGAS study (which stands for “Home-Based Exercise Program in the Indeterminate Form of Chagas Disease” in Portuguese) aims to evaluate the effects of a home-based exercise program on several physical and mental health parameters in individuals with indeterminate form of CD.

## Methods and analysis

### Study design

The PEDI-CHAGAS study is a two-arm (exercise and control) phase 3 superiority randomized clinical trial (trial registration REBEC UTN code U1111-1263-0153) that will be conducted at the Evandro Chagas National Institute of Infectious Diseases (INI- Fiocruz, Rio de Janeiro, Brazil). The INI-Fiocruz is a national reference center for treatment and research of infectious diseases and tropical medicine in Brazil that offers comprehensive care for individuals with CD through diagnosis, treatment, and rehabilitation services provided by a multidisciplinary team including physicians, nurses, nutritionists, social assistants, psychologists, pharmacists, physical therapists, physical education professionals, and health technicians. Approximately 900 patients with CD are currently under follow-up at the INI-Fiocruz clinic, of those about 300 have the indeterminate form of CD (45).

### Participants and recruitment

Patients with indeterminate form of CD, both sexes, will be consecutively invited by their assistant physicians to participate in the study. If they agree to participate, informed consent will be obtained, and visits will be scheduled in order to explain the procedures related to the research, and perform the evaluations of the variables that will be investigated in the study.

The inclusion criteria are: (1) serological positivity for CD by at least two different methods (ELISA, indirect immunofluorescence, immunochromatography, or chemiluminescence); and (2) having indeterminate CD defined by the absence of symptoms and/or signs of cardiac CD (normal or presence of non-specific CD abnormalities in ECG) and/or digestive CD. Clinical signs of cardiac CD will be assessed by ECG and echocardiographic (ECHO) evaluation. The ECG abnormalities compatible with cardiac CD are 2nd- and 3rd-degree right bundle-branch block, associated or not to left anterior fascicular block, frequent ventricular premature beats (VPBs > 1 by ECG), polymorphous or repetitive non-sustained ventricular tachycardia, 2nd- and 3rd-degree atrioventricular block, sinus bradycardia with heart rate less than 50 bpm, sinus node dysfunction, 2nd- and 3rd-degree left bundle-branch block, atrial fibrillation, electrical inactive area, or primary ST-T wave changes. ECHO abnormalities related to cardiac CD depends on the stage of the disease and may present as segmental left ventricular (LV) wall motion abnormalities (hypokinesia, dyskinesia, akinesia, small, or large aneurysms), LV dilatation, or global LV systolic dysfunction with diffuse hypokinesia (8). In terms of digestive presentation, patients without symptoms compatible with megacolon or megaesophagus will be considered without digestive CD and will not undergo contrasted examinations of the esophagus and colon.

The exclusion criteria are: (1) <18 years old; (2) evidence of non-CD cardiomyopathy; (3) musculoskeletal or cognitive limitations precluding physical exercise; (4) clinical contraindication for regular exercise; (5) regular physical exercise (1 × per week) in the previous 2 months; and (6) pregnancy.

### Outcomes

Participants will be assessed at baseline, and after three and 6 months of follow-up for all variables, except for echocardiogram exam and fasting blood tests that will be performed at baseline and after 6 months of follow-up. Two clinic visits within a 4-week period for each time point will be performed. The first clinic visit will consist of a clinical interview and physical examination, echocardiogram exam, fatigability evaluation, and cardiopulmonary exercise test. The second clinic visit will include fasting blood tests, nutritional interview, physical fitness evaluation, autonomic modulation assessment, and questionnaires to evaluate back pain, QoL, depression and anxiety, and sleep quality.

The primary outcome will be QoL. Secondary outcomes will include blood pressure, physical fitness components, nutritional status, fatigability, autonomic function, cardiac morphology and function, low back pain, depression and anxiety, stress, sleep quality, medication use and adherence, and biochemical, inflammatory, and cardiac biomarkers.

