#### Quality of life

Quality of life will be evaluated using the WHOQOL-Bref questionnaire, a generic instrument developed by the World Health Organization and validated for use in the Brazilian population (46). The questionnaire consisted of 26 questions, two items relate to general QoL (overall domain) and the other 24 encompassed in four domains (physical, psychological, social relationships and environment). Each domain is evaluated by scores ranging from 1 to 5, in which mean scores indicates the individual’s perception of each domain, where a higher score indicates a more positive perception.

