### Sample size

The sample size was calculated based on the findings by Carta et al. (73), which evaluated the effect of a physical exercise program on the QoL. In this study, there was a difference of 2.2 (± 2.1) points for the intervention group and 0.0 (± 3.2) point for the control group in the physical domain of the WHOQOL-Bref questionnaire (46). Assuming α = 0.05 and β = 0.10 and inflating the sample by 20% for eventual losses to follow-up, a total of 80 individuals will be necessary to perform the present study (40 in each group).

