### Statistical analysis

A dataset will be prepared including the information from all patients using the Redcap platform. Statistical analysis will be performed using Stata statistical software (version 13.0). The data analysis will comprise the estimation of the mean (standard deviations) for continuous and absolute frequency (percentages) for categorical variables. The effect of the home-based exercise program on the continuous variables over the intervention period will be determined using a linear mixed model. For categorical variables, generalized estimated equations with log link and binomial distribution will be performed to evaluate changes in the proportion of individuals between groups over the time. All measures performed in the intervention and control group will be used, regardless of losses to follow-up or compliance to the protocol during the intervention period, characterizing an intention-to-treat analysis. The variable of interest will be the interaction between time × treatment, which estimates the change rate of the outcome over time. Protocol analysis including only completers will also be performed. Adjustments for baseline prognostic variables will be made in case of unbalance distributions between the groups. A *p*-value < 0.05 will be considered significant for all statistical tests.

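### The primary outcome is named only as QoL, which the protocol describes as five WHOQOL-Bref scores; the trial is sized on one of them, and every test uses 0.05 without a multiplicity rule

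*Protocol article*

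**What the plan says.** - **Outcomes:** "The primary outcome will be QoL". No domain, summary score or deciding visit is attached to this. The assessment schedule is: "Participants will be assessed at baseline, and after three and 6 months of follow-up for all variables", with exceptions only for the echocardiogram and fasting blood tests.
- **Quality of life:** the instrument is WHOQOL-Bref, in which "two items relate to general QoL (overall domain) and the other 24 encompassed in four domains". The scores are separate: "Each domain is evaluated by scores ranging from 1 to 5". No total across domains is defined.
- **Sample size:** the planning effect is a change of 2.2 (SD 2.1) with exercise against 0.0 (SD 3.2) in control, "in the physical domain of the WHOQOL-Bref questionnaire". With α = 0.05, β = 0.10 and a 20% allowance for losses, this gives 80 participants, 40 per group.
- **Statistical analysis:** "The variable of interest will be the interaction between time × treatment, which estimates the change rate of the outcome over time". A p-value below 0.05 "will be considered significant for all statistical tests". No multiplicity rule is given.

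**The concern.** Three parts of the protocol do not fit together. The declared primary outcome is a concept measured by five scores. The sample size is a single comparison on one of those scores. The significance rule applies 0.05 to each test.

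Followed as written, a significant result on the psychological, social, environment or overall score could be reported as a positive primary result just as readily as one on the physical domain. The 5% error rate used for sizing would then not be the error rate of the primary claim. A choice of score made after results are known could not be shown to be independent of them, which matters for a trial described as phase 3 superiority.

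**Working it through.** **Inputs from the protocol.** Difference 2.2; SDs 2.1 and 3.2; α = 0.05; power 0.90; 20% loss; 1:1 allocation; five scores. The test's sidedness is not stated. Two-sided is assumed because it reproduces N; one-sided gives 26 per arm, 33 after losses, 66 in total.

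**1. Reproduce the stated sample size.**
- Sum of variances: 2.1² + 3.2² = 4.41 + 10.24 = 14.65. Root-mean-square SD: √(14.65/2) = 2.706.
- n per arm = (1.960 + 1.282)² × 14.65 / 2.2² = 31.8, rounded up to 32.
- Allowing for losses: 32/0.80 = 40 per arm, 80 in total. This matches the protocol.
- Power at 32 per arm: SE = √(14.65/32) = 0.677, and 2.2/0.677 = 3.251. Φ(3.251 − 1.960) = 90.2% by the normal approximation; a Welch t-test gives 89.1%.

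The sizing is therefore correct for one test of the physical domain at 0.05.

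**2. Error rate if any of five scores may carry the claim.**
- Independent scores: 1 − 0.95⁵ = 22.6%.
- Correlated scores: the probability that at least one of five equicorrelated normal test statistics exceeds 1.96 in absolute value. The protocol gives no correlations, so a range is assumed.

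| Assumed correlation between scores | Chance of at least one false positive |
|---|---|
| 0 | 22.6% |
| 0.3 | about 21% |
| 0.5 | about 18% |
| 0.7 | about 15% |
| 0.9 | about 10% |

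Even at 0.9 the rate is about twice the stated 5%.

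**3. Power if alpha were split equally over five scores** (0.05/5 = 0.01 each, assuming the physical-domain effect).
- 32 evaluable per arm: Φ(3.251 − 2.576) = 75.0% by the normal approximation; 71.7% by Welch.
- To restore 90%: (2.576 + 1.282)² × 14.65 / 2.2² = 45.04, rounded up to 46 evaluable per arm. Then 46/0.80 = 57.5, rounded up to 58 per arm, 116 in total instead of 80.

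**4. The other four scores.** The Sample size section gives no difference or SD for them, so no power can be computed from the document.

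**5. One named score.** With the physical domain as the only primary score and one contrast, step 1 applies unchanged: α = 0.05, about 90% power, N = 80.

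**The case against.** The strongest reply is that the protocol does not declare five co-primary outcomes; it leaves the score unspecified. The only score tied to the trial's planning hypothesis is the physical domain, and an analysis plan that is not shown may name it. It is true that five primary scores is a reading of an open definition, and the 10–23% applies only under that reading. But the protocol is where the primary outcome is fixed. This one pairs a multi-score outcome with a blanket 0.05 threshold, and nothing in it stops another domain from being reported as the primary result.

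Two stronger readings are tempting, and the document supports neither.

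- **That the 90% power is wrong.** It is not. It reproduces for the physical domain, and further unadjusted tests do not lower it. The 72–75% arises only under an alpha split that the protocol does not propose.
- **That each score is tested separately at 3 and 6 months, giving ten primary tests.** The Statistical analysis section names one quantity of interest per outcome, the time × treatment interaction, and states no separate visit tests. The supported count is five.

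One might also fault the interaction test itself, for loss of power if visit is categorical or for bias if time is linear. Either result depends on how time is coded and on the course of the effect, and a bias on when losses occur as well. The protocol states none of these, and the coding of time is commonly left to an analysis plan.

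**Conclusion.** The concern holds in this form: the primary outcome is not reduced to one score, the trial is sized on a score never named as primary, and the stated testing rule does not protect the 5% error rate for a primary claim about QoL. If any of the five scores may count, the familywise error is about 10–23%.

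That range assumes one two-sided test per score, no true effect on any score, and equal between-score correlations from 0 to 0.9, which are not in the protocol. The sample size and 90% power stand for the physical domain at unadjusted 0.05 and are unsupported for the other four scores. The planning figures are taken as given; the arithmetic needs only that the difference and the SDs share one scale.

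**What to change.** Before any outcome data are seen, amend the Outcomes, Sample size and Statistical analysis sections, and the registry entry, to state that:

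1. The single primary outcome is the WHOQOL-Bref physical domain.
2. The primary test is one pre-specified treatment contrast with one degree of freedom that matches the sizing, for example the treatment difference in change at 6 months from the mixed model. Another single contrast would also serve if the sizing is shown to apply to it.
3. The other three domains, the overall score and any 3-month contrast are secondary, without confirmatory claims.

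This is a change of wording. N = 80, alpha 0.05 and about 90% power are kept. The cost is that the other scores can no longer carry the primary claim. If the sponsor wants several scores to be able to do so, the protocol needs a stated multiplicity rule and a new sample size: an equal split over five scores would need 116 participants under the same planning effect.

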#### Quality of life

Quality of life will be evaluated using the WHOQOL-Bref questionnaire, a generic instrument developed by the World Health Organization and validated for use in the Brazilian population (46). The questionnaire consisted of 26 questions, two items relate to general QoL (overall domain) and the other 24 encompassed in four domains (physical, psychological, social relationships and environment). Each domain is evaluated by scores ranging from 1 to 5, in which mean scores indicates the individual’s perception of each domain, where a higher score indicates a more positive perception.

#### Blood pressure

Blood pressure measurements will be taken on the left arm with participants seated in a quiet room after 5 min rest using an Omron digital sphygmomanometer. The mean value between three measurements taken at 1-min interval will be considered (47).

#### Physical fitness components

##### Cardiorespiratory capacity

Cardiorespiratory capacity will be assessed by cardiopulmonary exercise test (CPET). The test will be performed in a temperature-controlled environment (18–2°C) using the VO2000 gas analyzer (MedGraphics^®^, St. Paul, MS, USA) with a computerized system Ergo PC Elite (Micromed^®^, Brasília, Brazil) and a treadmill (Inbramed^®^, Porto Alegre, Brazil). The 12-lead electrocardiogram will be recorded in addition to the sampling of the inhaled and expired gases breath by breath and averaged every 10 s. A blinded evaluator will perform an incremental exercise test using a ramp protocol, tailored to achieve a fatigue limited exercise duration of approximately 8–12 min (48). The exercise test workloads will be settled based on age, gender, height, and weight and adapted according to each individual physical condition and effort tolerance. The exam will be limited by symptoms using the Borg perceived effort scale in a range from 6 (no exertion at all) to 20 (maximum effort tolerated), seeking to achieve a respiratory quotient (R) reflecting the relationship between VCO_2_/VO_2_ greater than 1.10 (theoretical maximum effort). The examiner may interrupt the test in case of identification of any harmful clinical or hemodynamic response during the test. The recovery phase will be active with walking in a pre-determined velocity of 2 km.h^–1^ and 2% of inclination. The peak oxygen consumption (VO_2_ peak), which corresponds to the highest volume of oxygen extracted from the air inspired by pulmonary ventilation in a given period of time, calculated as the difference between the inspired and expired O_2_ volume (mL/kg/min) (48), will be evaluated. Other CPET variables including maximum heart rate (HR max), maximum blood pressure (BP max), oxygen consumption at anaerobic threshold (VO_2_ AT), oxygen pulse (O_2_ pulse), ventilation slope equivalent to carbon dioxide production (slope VE/VCO_2_), functional aerobic impairment (FAI), and oxygen uptake efficiency slope (OUES) values will also be evaluated.

